### Theoretical and practical counseling sessions

The practical counseling intervention program consists of eight distinct but interrelated modules that cover topics such as diabetes, free living PA and exercise and the psychology of behavior change. The exercise sessions (75 min each), held in three specialized gym facilities (see Additional file 1: Appendix A) and supervised by a certified exercise specialist, are geared to expand and put into practice the knowledge acquired during the theoretical counseling session. Each exercise session is composed of 30 min of aerobic exercise followed by 30 min of resistance exercise, plus additional 15 minutes for warm-up and cool-down (including stretching).

In these sessions, the exercise specialist improves the patient’s knowledge of the effects of exercise on patient’s own health, including both advantages and disadvantages; conditions under which exercise should not be done; difference between habitual and occasional exercise; essential parameters of wellness such as blood pressure (BP), heart rate (HR), and blood glucose. In addition, health instructions are given to identify the difference between aerobic and resistance exercise; evaluate the intensity of exercise; perform warm-up and stretching safely; monitor blood glucose correctly; and correct imbalances during and after the exercise session. A detailed list of the actions performed by the exercise specialist during the theoretical and practical counseling sessions is presented in Table 5.

**Table 5 Tab5:** List of the actions performed by the exercise specialist during the theoretical and practical counseling sessions

#	Action
1	Establishes clinical condition and physical fitness and identifies the adequate exercise protocol (using a homemade exercise algorithm) on the basis of previous evaluations.
2	Measures BP, HR, and glucose level before and after each exercise session and provides feedback to the subject on the effect of the specific exercise adopted.
3	Instructs the patient to perform these measurements, indicates the range of glycemic values allowing or contraindicating exercise, and suggests to start with resistance exercise when glycemia is on the low side of the range, especially for those treated with insulin or secretagogues.
4	Reviews with the patient the structure of the exercise session (warm-up, exercise, and cool-down phases), instructs on how to perform a safe warm-up and cool down, providing practical examples for the different exercise types, and stressing the importance of the gradualism of the increase and decrease of the intensity for the warm up and cool down, respectively.
5	Explains the difference between aerobic and resistance exercise, proving practical examples of the different exercise forms (endurance exercise machines, resistance exercise devices, free body exercises).
6	For aerobic exercise training, illustrates the correct exercise progression and control and, throughout the counseling sessions, encourages the patients to progressively increase the exercise intensity, instructing on how to identify and control light, moderate and vigorous intensity on the basis of breathing frequency (talk test), rate of perceived exercise, and HR. As an example, exercise intensity is explained on the basis of the ability to perform a conversation as follows: o light intensity: “allows to respond to conversation without problems.” o moderate intensity: “allows to carry on a conversation but with some difficulties.” o vigorous intensity: “ the speech is limited to short phrases.”
7	Especially for unsupervised PA/exercise and for patients with complications, advises the patients to work at low-to-moderate intensity, as it is the one allowing to reduce the risk of adverse events while providing substantial benefits.
8	With regard to the volume of aerobic exercise, gives examples on how to comply with the exercise recommendations on the minimum amount of PA/exercise providing health benefits, and stressing that adding more PA/exercise will results in additional benefits.
9	Describes the correct way of increasing training volume, augmenting first duration and then intensity, especially in patients with complications.
10	Explains the difference between weight bearing and non-weight-bearing exercise and the relevance for the subjects with complications, providing practical examples.
11	For resistance exercise training, provides examples on the exercise taxing the major muscle groups (eight to 10 exercises), explaining (and checking the learning of) the correct exercise technique, and illustrates a typical sequence of resistance exercises, alternating opposing muscle groups and/or upper and lower body exercises.
12	Explains the concept that a higher repetitions number corresponds to a light weight to be lifted (therefore lighter intensity) and vice versa, and teaches the correct breathing pattern during the different resistance exercises adopted, reminding that breath holding (Valsalva maneuver) should be avoided.
13	Instructs to perform multiples sets (for example, two to three sets) with adequate recovery between them (for example, 2 min), depending on the intensity adopted (less repetitions per set usually equal longer recovery time).
14	Identifies indicated and contraindicated resistance exercises on the basis of the specific patient’s complications.
15	Provides examples on how to substitute the typical exercises executed in the gym setting with other forms of PA/exercise to be performed outside the gym, reminding patients that new forms of unsupervised PA/exercise should be adopted after consulting the exercise specialist.
16	Helps the patient to organize a typical working day and weekend in order to find time and space for performing any type of PA (home, commuting, occupational, and LT), reduce the SED-time, and remove potential obstacles.
17	Assists the patient in setting behavior and outcome goals as well as in the choice of the indoor and outdoor PAs that are the most appealing and feasible.

*BP* blood pressure, *HR* heart rate, *PA* physical activity

### Standard care

Participants from the CON group receive general physician recommendations for increasing the amount of daily PA and decreasing the SED-time.

All patients receive a treatment regimen aimed at achieving optimal glycemic, lipid, BP, and body weight targets, as established by current guidelines [28]. This program eventually includes glucose-, lipid- and BP-lowering agents as needed and, when indicated, anti-platelet drugs, plus a dietary prescription, which is preceded by a preliminary nutritional evaluation with assessment of BMI and the individual patient requirements and preferences. The diet contains 55 % calories from complex carbohydrates, 30 % from fat, and 15 % from protein. Since all patients are overweight or obese, they receive a low-calorie diet (negative balance of 500 kcal/day, but not less than 1500 kcal in males and not less than 1200 kcal in females), calculated by adding the estimated energy expenditure from routine and voluntary PA to the basal metabolism estimated using the gas exchange analyzer FitMate (Cosmed, Rome, Italy). PA is calculated by multiplying the MET scores (one MET expresses an oxygen consumption, taken by convention to be 3.5 ml) of the various activities by the weekly hours spent in each of them, as reported in the Minnesota LTPA questionnaire, and expressed as METs ∙ h^−1^ ∙ week^−1^.

### Outcome measures

The primary objective of IDES-2 is to evaluate the incremental impact of intervention on the promotion and maintenance of a physically active lifestyle as well as on the reduction in SED-time.

Secondary objectives include testing the efficacy of the intervention on physical fitness, modifiable cardiovascular risk factors, musculoskeletal disturbances, well-being/depression, and health related QoL.

As physicians and exercise specialists are aware of group assignment, outcome assessment is also unblinded, except for biochemical testing at the central laboratory.

Matthews’ cut-points are used to identify the time spent in light intensity (100 to 1951 counts/min corresponding to 1.5 to 2.9 METs) [42], whereas Freedson’s cut-points are used to determine the time spent in PA of moderate intensity (1952 to 5724 counts/min corresponding to 3 to 5.9 METs) and vigorous intensity (≥5725 counts/min corresponding to ≥6 METs) [43]. The time spent in non-accelerometer-recordable PAs, as reported on the daily diary, is added to that recorded by the accelerometer, according to the intensity of each activity [44]. Moderate-intensity PA is combined with vigorous-intensity PA into the MVPAs, as participants spend little time in vigorous-intensity PA.

#### Assessment of physical fitness

Parameters of physical fitness, that is, cardiorespiratory fitness, strength and flexibility, are evaluated at baseline, 12 months, 24 months, and end-of-study. The tests are preceded by two consecutive run-in sessions to allow the patients to become familiar with the testing devices and protocols.

Cardiorespiratory fitness is assessed by a maximal treadmill exercise test using a Balke protocol [45]. The treadmill speed is set at 88 m/min and the grade is 0 % during the first minute, 2 % during the second minute, and is then increased every minute by 1 %; after 25 minutes, the treadmill grade is kept constant, whereas the speed is increased by 5.4 m/min every minute. Patients are instructed not to hold the treadmill rails and are verbally encouraged to reach volitional exhaustion, as reported by the patient or by the physician for medical reasons. The time to exhaustion is used to estimate the maximal oxygen uptake, given the high correlation between these two parameters [46].

For strength assessment, isometric muscle strength is measured by means of a strain gauge tensiometer (Digimax, Mechatronic GmbH, Germany), as previously described [47]. Isometric tests have been chosen since they are reproducible [48, 49], do not require complex execution technique, and can therefore be easily performed by both trained and untrained subjects. Lower limb muscle strength is assessed by maximal voluntary contractions (MVCs) performed at a costumed leg extension machine (Technogym). The angle at the knee and the hip is fixed at 90°. Upper body muscle strength is assessed by MVCs performed at a shoulder press (Technogym) along the sagittal plane, with a 90° and 45° angle at the elbow and between the upper arm and the trunk, respectively. These exercise modalities have been chosen in order to test muscle chains involved in the fundamental activities of daily living. In both tests, subjects are asked to exert their maximal force with both limbs simultaneously and to maintain it for at least 2–3 s before relaxing. For each exercise, three MVC are performed, with a 3-min rest interval between contractions. Participants are asked to perform additional contractions if the MVC of their last attempt exceeds the previous by at least 5 %. During the MVCs, verbal encouragement is provided, always by the same investigator for all subjects.

For hip and trunk flexibility assessment, a standard bending test is executed [27]. Standing on a step with legs fully extended, patients are asked to bend the torso forward to try to touch the ground with their fingertips. The test is performed three times and the distance between the finger and the ground is measured by the exercise specialist at the third attempt.

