With regard to possible risks of bias, we anticipate that, according to the Cochrane Collaboration [75], the risk of selection bias is low, due to the use of adequate methods for sequence generation and allocation sequence concealment, although patients who agree to participate in a lifestyle intervention program might be different from those who refuse. Moreover, though blinding of participants and investigators is impossible in exercise intervention studies, the risks of performance, detection, and attrition bias are also limited for several reasons. Regarding performance, despite the fact that independently of intervention, participants might be influenced by knowledge of group assignment in adopting and maintaining a physically active lifestyle, the possibility that unblinding to group assignment may result in an overestimation or an underestimation of intervention effects is low. On the one hand, subjects from the control group of the IDES performed a considerable amount of PA [14] and, though PA measurements are known to affect physical activity behavior [76], this would impact on PA volume of both groups. On the other hand, investigators are asked not to provide subjects from the control group with PA advice other than general recommendations for increasing the amount of daily PA (and decreasing the SED-time), and intensification of pharmacological treatment to compensate for lower PA in these individuals will be accounted for in the statistical analysis. Regarding detection, because the primary outcome and some secondary outcomes (physical fitness and cardiovascular risk factors) are objective, the risk of bias is low on both the participant’s and investigator’s side, although study subjects might be influenced by knowledge of group assignment when filling in questionnaires for musculoskeletal disturbances, well-being/depression, and health-related QoL. Regarding attrition, in the IDES, knowledge of group assignment did not affect remaining in the trial for the entire study period as participants from the control group dropped out at a rate and for reasons similar to those of the exercise group [14]. Moreover, as reported above, the risk of attrition bias due to missing data has been adequately prevented and will be treated according to a recent National Research Council report on the topic [57].

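### The Discussion calls physical fitness objective with low detection bias, but the fitness tests depend on voluntary effort and are assessed unblinded

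*Protocol article*

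**What the plan says.** Physical fitness is a secondary outcome (Outcome measures). The section on assessment of physical fitness describes three tests.

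- **Treadmill.** Patients "are verbally encouraged to reach volitional exhaustion, as reported by the patient or by the physician for medical reasons". The duration reached is then converted into an estimate of oxygen uptake.
- **Strength.** In isometric tests, "subjects are asked to exert their maximal force with both limbs simultaneously". During these contractions "verbal encouragement is provided, always by the same investigator for all subjects".
- **Flexibility.** In the bending test, "the distance between the finger and the ground is measured by the exercise specialist at the third attempt".

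On blinding, the Randomization section leaves participants, physicians and exercise specialists aware of the arm. Outcome measures adds: "As physicians and exercise specialists are aware of group assignment, outcome assessment is also unblinded". The only exception there is central laboratory testing.

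The risk-of-bias paragraph of the Discussion concludes: "because the primary outcome and some secondary outcomes (physical fitness and cardiovascular risk factors) are objective, the risk of bias is low". It applies this to both the participant and the investigator, and concedes an influence of known allocation only for the questionnaires.

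**The concern.** An outcome is protected from knowledge of the arm when neither the patient's will nor the assessor's conduct can move the recorded value. A stopwatch or a strain gauge gives an exact reading, but the quantity read here is how long a patient chooses to continue or how hard the patient chooses to push, with staff encouraging. The flexibility distance is a manual reading by a person who knows the arm.

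The arms also differ in their contact with the profession involved. Exercise specialists were trained both to assess fitness and to supervise sessions (Investigators), and they deliver the practical sessions to the intervention arm only. Table 5 has them encourage intervention patients to raise aerobic intensity and teach them to judge exertion.

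If the Discussion's statement stands, a between-arm fitness difference could be reported as a physiological effect with detection bias already ruled out, although the design does not rule it out.

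**Working it through.** **1. Can each test be influenced by knowledge of the arm?**

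| Test | What fixes the value | Stated safeguard | Blinded? |
|---|---|---|---|
| Treadmill time, converted to estimated oxygen uptake | Patient's decision to stop, or physician's for medical reasons, under encouragement | None for encouragement | No |
| Maximal voluntary contraction | Patient's effort, under encouragement; force read by tensiometer | Same investigator encourages all subjects; numeric rule for extra attempts | Not stated for this person; outside the laboratory exception |
| Bending test | Distance read by the exercise specialist | Third attempt used | No |

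Outcome measures exempts only laboratory tests from unblinded assessment, whereas the Discussion clears fitness as well. The two sections do not agree.

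**2. Does the baseline remove it?** Table 2 places the run-in sessions at R2 and R3. The Recruitment section lists the baseline fitness test at R4 before patients are told their group. Taking that order as the actual one, knowledge of the arm is absent at baseline and present at every follow-up test. The Statistical analysis section compares change from baseline, so an influence that appears only after baseline is not subtracted out. The run-in sessions equalize familiarity before allocation and do not act on it afterwards.

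**3. Contact with specialists before each test.** Eight sessions a year give 8, 16 and 24 sessions in the intervention arm by months 12, 24 and 36, and none in the control arm. Table 2 places the sessions in months 1, 13 and 25 and the fitness tests at months 12, 24 and 36, a gap of 12 − 1 = 24 − 13 = 36 − 25 = 11 months. The Follow-up section instead puts the intermediate fitness tests at F4 and F7 (months 16 and 28), a gap of 16 − 13 = 28 − 25 = 3 months. The two schedules need reconciling. On either, the last test falls about 11 months after the last sessions.

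**4. Size.** The documents give no SD and no expected effect for fitness. The only sample size figure is for daily physical activity: 0.15 × 24.2 = 3.63; 3.63 / 9.4 = 0.386 SD. An unpaired t-test at two-sided 0.05 and 90% power then needs 141.9, so 142 per arm, as stated. That figure is sound and is used below only for the number of patients.

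For illustration, assume no true effect, n = 142 per arm, and a systematic between-arm difference of b SD arising from effort, encouragement or reading. With s = b × √(n/2) = b × √71, the chance of a significant result at two-sided 0.05 is 1 − Φ(1.96 − s) + Φ(−1.96 − s).

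| Assumed b (SD) | s | Chance of a significant result |
|---|---|---|
| 0 | 0 | 5% |
| 0.05 | 0.42 | 7% |
| 0.10 | 0.84 | 13% |
| 0.20 | 1.69 | 39% |
| 0.30 | 2.53 | 72% |

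The values of b are assumptions. The table shows how sensitive the test is to such a bias. It does not estimate the bias.

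**The case against.** The strongest reply is that the article is open about unblinded assessment, explains that blinding is not feasible, and already limits the problem. One investigator encourages all subjects in the strength tests. The rule for extra contractions is numeric and the same in both arms, and force is read by an instrument. Under Table 2 the supervised sessions end about 11 months before each fitness test. The accelerometer primary outcome and the sample size are not involved. All of this is correct. A single encourager limits variation between testers, but does not remove bias if that person knows the arm, and no such safeguard is stated for the treadmill.

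A reader might also infer four stronger points that the documents do not support.

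- *That encouragement is unscripted.* No script is described, but a condensed article may leave one to the full protocol, so silence is no evidence.
- *That each patient is tested by his or her own coach.* The specialist is named as tester only for flexibility. For the other tests the article describes training in fitness assessment, not who runs which test.
- *That the bias favors the intervention arm.* This is plausible given the contact pattern, but nothing in the documents shows it. When discussing performance bias, the article itself considers both over- and underestimation.
- *That one extra treadmill minute raises fitness by about 8% to 12%.* This rests on assumed stopping times of 8 to 12 minutes (1/12 = 8%, 1/8 = 12.5%). It describes time rather than oxygen uptake, and the conversion equation is not given.

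**Conclusion.** The point holds as a contradiction within the article. The Discussion's low rating of detection bias for fitness does not fit an unblinded assessment of two effort-dependent tests and one manual reading, and the pre-allocation baseline does not cure it. The conclusion rests on the article's own description of the tests and of who knows the arm, and on the order of events listed for R4. It does not depend on whether an encouragement script exists or on who tests whom.

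Direction and size are unknown. The effect is confined to the fitness outcomes, which are secondary, and it does not show that any fitness result will be wrong. It means that a fitness difference cannot be presented as protected from detection bias. The point is worth correcting but does not threaten the trial's main conclusion.

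**What to change.** 1. In the Discussion, move physical fitness to the outcomes open to detection bias, and interpret fitness differences accordingly in the report. This costs one sentence.
2. At the end of every treadmill test, record peak heart rate and perceived exertion and compare them by arm as a check on effort. This costs two values per test. Heart rate should carry more weight, because perceived exertion is the patient's own rating and intervention patients are taught to judge exertion (Table 5).
3. Use the same encouragement wording in both arms. If the full protocol already fixes it, cite it.
4. Where existing staffing allows, have the treadmill and flexibility tests run by a specialist who did not coach that patient. This costs some scheduling. Keep the single investigator for strength, since rotating testers there would give up a safeguard the protocol already has.

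Where a gym cannot separate coach and tester, items 1 to 3 still apply. Recruitment was ongoing at manuscript submission, so tests still to come at that point could follow the change.

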#### Assessment of modifiable cardiovascular risk factors

The following modifiable cardiovascular risk factors are being evaluated at baseline, end-of-study, and every 4 months in-between: HbA_1c;_ fasting plasma glucose (FPG); serum insulin; C-peptide; BMI; waist circumference; body composition; BP; triglycerides; total, LDL and HDL cholesterol; high sensitivity-C-reactive protein (hs-CRP); aspartate aminotransferase (AST); alanine aminotransferase (ALT); γ-glutamyl-transpeptidase (γ-GT); creatine kinase (CK); complete blood count; uric acid; blood urea nitrogen (BUN); serum creatinine; urinalysis; and albumin/creatinine ratio on first-voided urine samples.

Body weight and height are measured using a scale and stadiometer, and BMI is then calculated as weight (kg)/height (m^2^), whereas waist circumference is taken at the umbilicus. Body composition is evaluated by assessing the fat mass and fat-free mass by the use of a body fat monitor (Tanita BF664, Vernon Hills, IL, USA). BP is recorded with a sphygmomanometer after a 5-minute rest while the patient remains seated with the arm at the heart level.

Biochemical tests are centralized at the Laboratory of Clinical Chemistry of Sant’Andrea Hospital, an accredited and ISO9001 certified structure, using standard analytical techniques (Table 6). The Homeostasis Model Assessment-Insulin Resistance (HOMA-IR) index is calculated from the FPG and insulin levels [50]. The glomerular filtration rate (GFR) is estimated from the serum creatinine by the use of the Chronic Kidney Disease Epidemiology Collaboration (CKD-EPI) equation [51]. Global and fatal CHD 10-year risk scores are calculated using the United Kingdom Prospective Diabetes Study (UKPDS) risk engine [52].

**Table 6 Tab6:** Laboratory tests

Analyte	Method	Manufacturer
HbA_1c_	HPLC (Adams TMA1C HA-8160)	Menarini Diagnostics, Florence, Italy
FPG	VITROS 5,1 FS Chemistry System	Ortho Clinical Diagnostics Inc, Raritan, NJ, USA
Insulin	Chemiluminiscent immunometric assays (Immulite 2000 Thes)	Diagnostic Products Corporation, Los Angeles, CA, USA
C-peptide	Chemiluminiscent immunometric assays (Immulite 2000 Thes)	Diagnostic Products Corporation, Los Angeles, CA, USA
Triglycerides	VITROS 5,1 FS Chemistry System	Ortho Clinical Diagnostics Inc, Raritan, NJ, USA
Total cholesterol	VITROS 5,1 FS Chemistry System	Ortho Clinical Diagnostics Inc, Raritan, NJ, USA
LDL cholesterol	VITROS 5,1 FS Chemistry System	Ortho Clinical Diagnostics Inc, Raritan, NJ, USA
HDL cholesterol	VITROS 5,1 FS Chemistry System	Ortho Clinical Diagnostics Inc, Raritan, NJ, USA
hs-CRP	VITROS 5,1 FS Chemistry System	Ortho Clinical Diagnostics Inc, Raritan, NJ, USA
AST	VITROS 5,1 FS Chemistry System	Ortho Clinical Diagnostics Inc, Raritan, NJ, USA
ALT	VITROS 5,1 FS Chemistry System	Ortho Clinical Diagnostics Inc, Raritan, NJ, USA
γ-GT	VITROS 5,1 FS Chemistry System	Ortho Clinical Diagnostics Inc, Raritan, NJ, USA
CK	VITROS 5,1 FS Chemistry System	Ortho Clinical Diagnostics Inc, Raritan, NJ, USA
Complete blood count	VITROS 5,1 FS Chemistry System	Ortho Clinical Diagnostics Inc, Raritan, NJ, USA
Uric acid	VITROS 5,1 FS Chemistry System	Ortho Clinical Diagnostics Inc, Raritan, NJ, USA
BUN	VITROS 5,1 FS Chemistry System	Ortho Clinical Diagnostics Inc, Raritan, NJ, USA
Serum creatinine	VITROS 5,1 FS Chemistry System	Ortho Clinical Diagnostics Inc, Raritan, NJ, USA
Urinary albumin	mAlb VITROS	Ortho Clinical Diagnostics Inc, Raritan, NJ, USA
Urinary creatinine	VITROS 5,1 FS Chemistry System	Ortho Clinical Diagnostics Inc, Raritan, NJ, USA

Biochemical measurements in the IDES-2

*IDES* Italian Diabetes and Exercise Study, *HbA*
_*1c*_ hemoglobin A_1c_, *HPLC* high-performance liquid chromatography, *FPG* fasting plasma glucose, *hs*-*CRP* high sensitivity-C-reactive protein, *AST* aspartate aminotransferase, *ALT* alanine aminotransferase, *γ*-*GT* γ-glutamyl-transpeptidase, *CK* creatine kinase, *BUN* blood urea nitrogen

